## Abstract

**Background:** Clinical trials of non-vitamin K antagonist oral anticoagulants (NOACs) in patients with chronic heart failure and atrial fibrillation (AF) have demonstrated reduced risks of stroke and bleeding compared with vitamin K antagonists (VKAs). Here, we aim to assess the clinical efficacy and safety of rivaroxaban, a NOAC, compared with warfarin, a VKA, and the effects of rivaroxaban on cardiovascular biomarkers in patients with acute decompensated heart failure (ADHF) with reduced ejection fraction (≤40%) and AF.

**Methods:** Rivaroxaban Once-daily vs. dose-adjusted vitamin K antagonist on biomarkers in Acute Decompensated Heart Failure and Atrial Fibrillation (ROAD HF-AF) is a randomized, open-labeled, controlled, prospective, multicenter pilot study designed to assess cardiovascular biomarkers and the safety of rivaroxaban (20 or 15 mg in patients with creatinine clearance 30–49 mL/min per day) compared with VKA (target international normalized range: 2–3) in 150 patients hospitalized with ADHF and AF. The primary endpoint is the change in circulating high-sensitivity cardiac troponin (hsTn) during hospitalization. The secondary endpoints are bleeding, hospital stay duration, in-hospital mortality, and changes in cardiovascular, renal, and thrombosis biomarkers. Patients will be followed for 180 days.

**Conclusion:** We hypothesize that rivaroxaban will reduce myocardial injury and hemodynamic stress, as reflected by the biomarker status, within 72 h in patients with ADHF and AF, compared with VKA. We hope to facilitate future biomarker-based, large-scale outcome trials using NOACs in patients with ADHF and AF, based on the results of this multicenter, randomized, controlled study.

## Introduction

The prevalence of heart failure (HF) is rapidly increasing and is the leading cause of hospitalization in people aged over 65 years in developed countries (1, 2). Acute decompensated heart failure (ADHF) is a significant public health issue due to the substantial morbidity and mortality rates, including a high hospital readmission rate. Hypercoagulability is suggested as a risk factor for poor outcomes in patients with ADHF. For example, in a community-based study in the United States, ischemic stroke incidence was significantly higher in patients with HF than in the general population in the first 30 days after HF diagnosis and remained high during a 5-year follow-up (3). The prevalence of atrial fibrillation (AF) in patients with HF is high, and AF is the main factor driving the high incidence of thromboembolic events (4). Furthermore, comorbidities and factors that increase the risk of thromboembolic events in patients with AF, including old age, coronary artery disease, hypertension, and diabetes, are common in patients with both compensated and decompensated HF (5). Therefore, optimal anticoagulation is a potential strategy to improve outcomes in patients with ADHF.

Traditionally, vitamin K antagonists (VKAs), such as warfarin, are recommended to reduce thromboembolic event risk in patients with AF and HF. However, VKAs are limited by their interactions with other drugs and diet. Importantly, drug levels are influenced by the worsening renal function, liver congestion, and hemodynamic alterations observed in patients with ADHF. Non-vitamin K antagonist oral anticoagulants (NOACs), including rivaroxaban, apixaban, dabigatran, and edoxaban, are alternatives to VKAs, and they have demonstrated improved efficacy for stroke prevention and safety compared with VKAs in patients with HF and AF (6, 7). The benefits of NOACs compared with VKAs include fewer food and drug interactions and fixed dosing. Recently, the inhibition of thrombin generation has been suggested as a potential benefit of NOACs, especially rivaroxaban (8, 9). Thrombin is a key component in the coagulation pathway, and it enhances platelet activation and aggregation; thus, direct inhibition of the common pathway by antithrombotic therapy may mitigate ongoing myocardial injury in patients with ADHF (9). A *post-hoc* analysis of the COMMANDER HF trial demonstrated that 2.5 mg rivaroxaban twice daily significantly reduced stroke or transient ischemic attack (TIA) rate compared with placebo in chronic HF patients with coronary artery disease and sinus rhythm following recent worsening episodes (10). However, the clinical efficacy and safety of rivaroxaban in patients with ADHF and AF are unknown.

In patients with ADHF, biomarker analysis is utilized for accurate diagnosis and prognostication. Furthermore, biomarkers can provide valuable information on the pathophysiology of ADHF and the mechanism underlying the treatment effects (11). Therefore, it would be reasonable and informative to assess the potential benefits of rivaroxaban on myocardial and renal damage compared with VKAs, using surrogate biomarkers in hospitalized patients with ADHF and AF, in addition to the clinical efficacy and safety outcomes. In patients with ADHF, numerous cardiovascular biomarkers can be used to reflect hemodynamic stress and myocardial injury resulting from inflammation, neurohormonal and endothelial dysfunction, and microvascular thrombosis (11). Recently, high-sensitive troponin (hsTn) has emerged as a novel prognostic marker in patients with ADHF (12). Coronary microvascular dysfunction has been reported to be correlated with hsTn in patients with non-ischemic HF (13). In a sub-study of the RELAX-AHF trial, an increase in hsTn was related to poor clinical outcomes in patients with ADHF (14). Additionally, *post-hoc* analyses of the Val-HeFT and GISSI-HF trials demonstrated the clinical importance of ongoing myocardial injury in patients with HF (15). Specifically, increased plasma hsTn level was predictive of an increased risk of all-cause mortality in patients with HF. Therefore, ongoing myocardial injury, reflected by elevated plasma hsTn level, is a substantial risk factor for patients with ADHF, and this may be related to microvascular thrombosis. However, evidence demonstrating the benefit of antithrombotic therapy with direct factor Xa inhibition in patients with ADHF is lacking. Therefore, in the Rivaroxaban Once-daily vs. dose-adjusted vitamin K antagonist on the biomarkers in Acute Decompensated Heart Failure and Atrial Fibrillation (ROAD HF-AF) study, we will examine the potential beneficial effects of rivaroxaban vs. warfarin in patients with ADHF with reduced ejection fraction (EF) and AF.

## Study Design

### Overall Design and Ethics Approval

ROAD HF-AF is a prospective, multicenter, randomized, parallel-group, open-label exploratory study designed to assess the efficacy and safety of rivaroxaban compared with warfarin using the change in surrogate biomarkers in patients with ADHF and AF (Figure 1). Patients will be followed during and after hospitalization for 6 months. The study will be conducted in accordance with the International Conference on Harmonization Good Clinical Practice guidelines and principles in the Declaration of Helsinki. Written informed consent will be obtained from patients before study entry. The study has been approved by the institutional review board of each participating center (No. 4-2017-0776). The study is sponsored by Bayer Pharma (Berlin, Germany) and registered at clinicaltrials.gov (NCT03490994).

**Figure 1 F1:**
[figure not shown]
Study design. ADHF, acute decompensated heart failure; HD, hospital day; LMWH, low molecular weight heparin. ^*^Patients with an estimated glomerular filtration rate using the chronic kidney disease epidemiology collaboration (CKD-EPI) equation of 30–49 mL/min/1.73 m^2^ will receive 15 mg once daily.

### Objectives and Endpoints

The primary study objective is the maximum change in the hsTn level over 72 h from admission following treatment (Table 1). The maximum change in hsTn is defined as the greatest change from the natural log-transformed baseline hsTn value to the natural log-transformed peak hsTn value during hospitalization. The secondary objectives are the: (1) change in the hsTn level 30 and 180 days after treatment with rivaroxaban or warfarin [target international normalized ratio (INR): 2–3]; (2) change in D-dimer level during and after hospitalization as a thrombogenicity marker; (3) change in other biomarkers of cardiac fibrosis [soluble ST2 (sST2) and galectin-3], renal injury [cystatin C, neutrophil gelatinase-associated lipocalin (NGAL), and N-acetyl-β-D-glucosaminidase (NAG)], and thrombogenicity [thrombin–antithrombin (TAT) complex and plasminogen activator inhibitor type 1 (PAI-1)], hs-CRP, and NT-proBNP during and after hospitalization; (4) incidence and rate of major bleeding according to the International Society on Thrombosis and Haemostasis criteria (16) (e.g., bleeding causing a decrease in hemoglobin level of ≥2 g/dL; bleeding leading to transfusion; symptomatic bleeding in critical areas including intracranial, intraspinal, intraocular, pericardial, intraarticular, intramuscular with compartment syndrome, and retroperitoneal; and fatal bleeding causing death) or minor bleeding event during and after hospitalization; (5) hospital stay duration at initial hospitalization; (6) incidence of all-cause mortality during hospitalization and at 180-day follow-up; and (7) incidence of all-cause mortality and rehospitalization during hospitalization and at 180-day follow-up.

**Table 1 T1:** Study endpoints.

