**Primary endpoint**
• Change in hsTn over 72 h from admission after treated with rivaroxaban or warfarin

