#### Analyses

As the current study is not powered for clinical hypothesis testing, statistical analyses will be explorative and descriptive. All variables will be analyzed descriptively: categorical variables will be presented as frequency tables (absolute and relative frequencies with 95% CI) and continuous variables by summary statistics (mean, standard variation, minimum, median quartile, and maximum, and 95% CI). We will analyze circulating hsTn and other quantitative biomarkers with natural log-transformation, and the geometric mean with 95% CI will be provided for each visit. The adjusted geometric means of the maximum change in hsTn from the baseline to hospitalization will be evaluated using an analysis of covariance model, with the value at admission as a covariate, and stratification factors used for randomization and treatment as a factor. The treatment geometric mean ratio, which reflects the treatment difference between rivaroxaban and warfarin, as well as its 95% CI, will also be provided.

A survival analysis will be performed to describe the time from hospital admission to the composite endpoint, including all-cause mortality and rehospitalization. Kaplan–Meier estimates and plots will be obtained for each treatment. The hazard ratio for rivaroxaban over warfarin and its 95% CI will be generated from the Cox-proportional model. The incidence of all-cause mortality during hospitalization will be summarized in a frequency table with the corresponding percentage and 95% CI. The incidence of major and minor bleeding events during the study will be summarized in a frequency table with percentage and corresponding 95% CI. To adjust variations in treatment duration during the study, the incidence rate (number of patients with bleeding events divided by the cumulative person-time on treatment) will also be provided.

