### Early Effect of Rivaroxaban on Circulating hsTn Levels in Hospitalized Patients With Acute Decompensated HF

Troponin (Tn) level is frequently elevated in patients with ADHF, even without clinically evident coronary artery disease (20). The circulating troponin (cTn) level has been reported to be a reliable prognostic marker for short- and long-term outcomes in patients with ADHF (21, 22). Furthermore, studies on serial cTn measurements throughout hospitalization reported that patients with persistently elevated cTn had a worse prognosis than those without persistently elevated cTn (23). More recently, in a subgroup analysis of the RELAX-AHF study (19), the peak change in hsTn was found to be an independent risk predictor for cardiovascular death or renal injury/HF hospitalization and cardiovascular mortality up to 6 months. We will evaluate the benefit of rivaroxaban compared with VKAs using the peak change in hsTn in patients with ADHF and AF during hospitalization. According to RELAX-AHF study, the peak value of high hsTn was measured at day 2–day 5. Therefore, measuring the maximum change in the hsTn level over 72 h from admission as a primary endpoint would be reasonable.

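### The primary endpoint has two incompatible windows, 72 h from admission and the whole hospital stay, so the samples that form the peak hsTn are not fixed

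*Protocol article*

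**What the plan says.** Two consecutive sentences of Objectives and Endpoints give different windows. The objective reads: "The primary study objective is the maximum change in the hsTn level over 72 h from admission following treatment". The definition that follows is "the greatest change from the natural log-transformed baseline hsTn value to the natural log-transformed peak hsTn value during hospitalization".

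The split runs through the rest of the article:

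| Place | Window |
|---|---|
| Objectives and Endpoints, objective | 72 h |
| Table 1, primary endpoint: "Change in hsTn over 72 h from admission after treated with rivaroxaban or warfarin" | 72 h |
| Hypotheses in the Abstract and Conclusions | onset within 72 h |
| Discussion of the early effect on hsTn, last sentence | 72 h |
| Objectives and Endpoints, definition | hospital stay |
| Abstract, Methods: "The primary endpoint is the change in circulating high-sensitivity cardiac troponin (hsTn) during hospitalization" | hospital stay |
| Sample Size, drop-out sentence | hospital stay |
| Analyses, ANCOVA: "The adjusted geometric means of the maximum change in hsTn from the baseline to hospitalization will be evaluated using an analysis of covariance model" | hospital stay |
| Discussion of the early effect on hsTn, earlier sentence | hospital stay |

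The Study Protocol section and Table 3 place in-hospital visits, each with central laboratory tests, on D1, D2, D4 and D7, or at discharge if that comes before D7. No sentence says which window governs or which visits supply the peak.

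**The concern.** A maximum depends on how many samples it is taken over and when they are drawn. The sentence that produces the primary result, the ANCOVA, carries no 72 h limit. An analyst who follows it as written would therefore estimate something other than the stated objective and the hypothesis of an effect within 72 h.

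Under the hospital-stay window, the time of the last sample also depends on the discharge date, and so does whether it adds anything to D2 and D4. Length of stay is itself a secondary endpoint, and treatment is open-label. With both definitions in the text, either could be reported as primary once the data are known.

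**Working it through.** **1. The plan's own figure.** Sample Size gives a log-scale SD of 0.75, 75 patients per arm and a maximum imprecision of 18% for the geometric mean. Check: exp(1.96 × 0.75 / √75) − 1 = exp(0.1697) − 1 = 18.5%. The figure reproduces to within one percentage point. It rests on a baseline SD and is the same under either window, so it does not help to choose between them.

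**2. Samples in each window.** Take D1 as the day of admission.
- 72 h: D2 and, approximately, D4. Clock times are not given, so a D4 sample may fall slightly before or after 72 h.
- Hospital stay: D2, D4 and D7/discharge.

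**3. Does the rationale settle it?** The Discussion reports from the reference trial that "the peak value of high hsTn was measured at day 2–day 5" and concludes that 72 h is reasonable. Counting from D1, 72 h ends at about D4, so the cited range runs past the chosen window. It supports neither window cleanly.

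**4. Size within an arm (assumed inputs).** The article gives no within-patient variability for hsTn. Assume independent errors on the log scale with SD σ, samples 1, 3 and 6 days after baseline, and a linear trend b per day.
- With b = 0, the expected maximum is σ/√π = 0.564σ for two samples and 3σ/(2√π) = 0.846σ for three, a difference of 0.282σ. At σ = 0.4, exp(0.113) − 1 is about 12%. The third sample is the peak in one third of patients.
- With σ = 0.2 and b = −0.06, simulation of 400,000 patients gives a rise of about 1%. The third sample is the peak in about 8% of patients.
- Over σ = 0.2 to 0.4 and b = 0 to −0.06, the rise is about 1% to 12% and the share about 8% to 33%.

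A second model has no trend, σ = 0.2 to 0.5 and correlation ρ = 0.3 to 0.8 between samples. The rise is exp(0.282σ√(1−ρ)) − 1, or about 2.5% (σ = 0.2, ρ = 0.8) to 12.5% (σ = 0.5, ρ = 0.3).

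**5. Effect on the treatment ratio (illustration only).** If sampling and time course are alike in both arms, the shift in step 4 cancels. It does not cancel if the effect varies over time. Under the second model:

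| Assumed true effect | Ratio, 72 h window | Ratio, hospital-stay window |
|---|---|---|
| 0.80 on D2 and D4 only | 0.80 | about 0.88 to 0.93 |
| 0.80 on D7/discharge only | 1.00 | about 0.94 to 0.98 |

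**6. Unequal sampling.** Suppose the share of patients with a third sample differs by 20 percentage points between arms. The log ratio then moves by 0.2 × ln(1.01) = 0.002 to 0.2 × ln(1.12) = 0.023, or about 0.2% to 2.3%. For scale, using the baseline SD of 0.75 with 75 per arm and no covariate adjustment, the 95% CI of the ratio extends exp(1.96 × 0.75 × √(2/75)) − 1 = 27% above the estimate.

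**The case against.** The strongest reply is that the texts can be reconciled. The 72 h limit is the specific term: it stands in the objective, in Table 1, in both hypotheses and in the only sentence that justifies the endpoint. Mention of the hospital stay may serve only to separate the in-hospital peak from the secondary changes at 30 and 180 days. This stands as a reason to prefer 72 h. It does not remove the contradiction, because the nesting is stated nowhere and neither the formal definition nor the ANCOVA sentence carries the limit. An analysis plan, which is not shown, may list the visits, but it would still have to override one of the two stated definitions.

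Several stronger readings are tempting, and the article does not support them:
- **The 1% to 12% shift as a bias in the treatment effect.** It is a shift within an arm and largely cancels in the ratio. Nor can it be set against the plan's 18%, which is the sampling imprecision of one arm's geometric mean.
- **Enoxaparin until INR 2 as a cause of longer stays and more samples under warfarin.** No passage says that discharge waits for the INR. A stay beyond D7 adds no in-hospital sample, and step 6 suggests that the effect would be small.
- **Table 1 as a further definition because it omits the word maximum.** The objective cites Table 1 in the same sentence and the term is defined in the next, so this is shorthand.
- **A formal error-rate problem.** Analyses says that the study is descriptive and not powered for hypothesis testing. Central measurement of the biomarkers also limits the influence of open-label treatment on the assay itself.

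**Conclusion.** The contradiction is real. It lies in what the article states, not in what a condensed article leaves out. The two windows select different samples, and following the ANCOVA text would give a different variable from the one in the objective and hypothesis.

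The effect on the reported geometric mean ratio cannot be derived from the article. It is near zero if sampling and time course match between arms. It could be material if the effect is confined to one part of the stay, and an early effect is what the trial hypothesizes. The ranges in steps 4 to 6 rest on assumed SDs, trends, correlations and effect patterns. Because the windows share D2 and D4, the two results may agree in many patients.

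The trial is exploratory, so what is at stake is one unfixed primary estimate, intended to inform larger trials, and room to choose the definition after the data are seen.

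**What to change.** Use one window throughout. As 72 h is the specific term in the objective, Table 1 and the hypothesis:

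- Define the primary variable as max(ln hsTn at Visit 2 [D2], ln hsTn at Visit 3 [D4]) − ln hsTn at baseline (Visit 1).
- State a visit window around 72 h for the D4 sample, and a rule for patients with no Visit 3 sample because they were discharged earlier.
- Use this variable in the ANCOVA, in place of "maximum change in hsTn from the baseline to hospitalization".
- Report the peak that includes the D7/discharge sample as a sensitivity analysis.
- Align the Abstract, both sentences in Objectives and Endpoints, Table 1, Sample Size, Analyses and the Discussion of the early effect. There, say how the cited day 2 to day 5 peak timing supports a window that closes at about D4.

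If the sponsor did intend the whole stay, the same alignment is needed the other way, with the contributing visits listed. Either choice should be fixed before hsTn results are seen by arm. The cost is wording in the protocol and analysis plan; the scheduled visits already supply the samples, and no more patients are needed.

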**Primary endpoint**
• Change in hsTn over 72 h from admission after treated with rivaroxaban or warfarin
**Secondary endpoint**
• Change in hsTn from the baseline following hospitalization and 30 and 180 days after treatment with rivaroxaban or warfarin • Change in D-dimer from the baseline during and after hospitalization (Days 2, 4, and 7 or discharge, and 30 and 180 days after discharge) • Change in other biomarkers, including TAT complex, PAI-1, hs-CRP, NT-proBNP, sST2, galectin-3, cystatin C, NGAL, and NAG from baseline during (Day 7 or discharge) and after hospitalization (30 and 180 days after discharge) • Incidence and rate of major/minor bleeding events during and after hospitalization • Length of hospital stay at initial hospitalization • Incidence of all-cause mortality during and after hospitalization • Incidence of all-cause mortality and rehospitalization during the 180-day follow-up

*hsTn, high-sensitive troponin; TAT, thrombin–antithrombin complex; PAI-1, plasminogen activator inhibitor type 1; hs-CRP, high-sensitivity C-reactive protein; NT-proBNP, N-terminal proBNP; sST2, soluble ST2; NGAL, neutrophil gelatinase-associated lipocalin; NAG, N-acetyl-β-D-glucosaminidase*.

### Data Monitoring and Study Management

A Data Safety Monitoring Committee (DSMB) composed of independent experts, will be responsible for overseeing patient safety. Study sites will be randomly monitored at least once a year. During site visits, the monitors will review protocol compliance to ensure that data are obtained for all eligible patients and verify source documents. All clinical events, including hospitalizations and deaths, will be monitored and verified by an adjudication committee, composed of independent experts. The adjudication committee will be composed of 2 independent experts and one chairperson. A disagreement will be reviewed by the two reviewers and tried to be resolved. If the two adjudicators disagree, the chairperson will receive the material together with both proposals and will select one proposal, overruling the other (17).

### Participants

The study population will comprise ADHF patients with AF who have reduced EF and are hospitalized with a primary diagnosis of ADHF. The eligible patients at 10 participating hospitals in South Korea who meet all eligibility criteria will be considered for enrolment. Detailed inclusion and exclusion criteria are shown in Table 2. The participants will be included if they meet all the following criteria: (1) hospitalized adult patients (≥19 years old) with a primary diagnosis of ADHF; (2) non-valvular atrial fibrillation patients, as documented on electrocardiography, with CHA_2_DS_2_-VASc Score of 2 or more; 3) a diagnosis of HF with reduced EF confirmed by a left ventricular EF of ≤40% using transthoracic echocardiography at the time of admission or within 1 year from the point before admission; and (3) meet at least one of the following criteria: dyspnea at rest, tachypnea (respiratory rate > 20/min), rales, or pulmonary edema on chest X-ray. Participants will be excluded from the study if they have a history of increased bleeding risk (e.g., major surgical procedure or trauma within 30 days; history of major bleeding; clinically significant gastrointestinal bleeding within 180 days; chronic hemorrhagic disorder; intracranial neoplasm, arteriovenous malformation, or aneurysm; platelet count of <90,000/μL), have a contraindication to anticoagulation therapy, have a diagnosis of acute coronary syndrome at the time of admission, are planned for percutaneous coronary intervention, coronary artery bypass graft surgery, or another invasive cardiac intervention (e.g., catheter ablation, pacemaker, cardiac resynchronization therapy, and implantable cardiac defibrillator implantation), are currently on dual antiplatelet therapy (aspirin and adenosine-diphosphate receptor antagonist) or single antiplatelet therapy with a novel antiplatelet agent (e.g., ticagrelor, prasugrel) or warfarin with INR > 2, have cardiogenic shock [systolic blood pressure (SBP): <80 mmHg], creatinine clearance <30 mL/min using creatinine-based Chronic Kidney Disease Epidemiology Collaboration (CKD-EPI) equations, elevated liver enzymes (three-times the upper limit) or liver cirrhosis, uncontrolled hypertension (SBP > 180 mmHg), an allergy, adverse drug reaction, hypersensitivity to rivaroxaban or warfarin, have a life expectancy of <6 months (e.g., metastatic cancer), or are women who are pregnant or of child-bearing age.

**Table 2 T2:** Inclusion and exclusion criteria.

**Inclusion criteria**	**Exclusion criteria**
• 19 years of age or older • Hospitalized patients with a primary diagnosis of ADHF • Non-valvular atrial fibrillation patients, as documented on electrocardiography, with CHA_2_DS_2_-VASc Score of 2 or more • Diagnosis of heart failure with reduced ejection fraction confirmed by left ventricular ejection fraction of ≤40% at the time of the admission or within 1 year from the admission • At least one of the following: i Dyspnea at rest ii Tachypnea (respiratory rate > 20/min) iii Rales iv Pulmonary edema on chest X-ray	• History of increased bleeding risk* • Contraindication to anticoagulation therapy • Acute coronary syndrome diagnosis at the time of the admission • Planned for percutaneous coronary intervention, coronary artery bypass graft surgery, or other cardiac invasive interventions (e.g., catheter ablation, pacemaker, CRT, ICD implantation) • Currently on dual antiplatelet therapy (aspirin and ADP receptor antagonist) or single antiplatelet therapy with a novel antiplatelet agent (e.g., ticagrelor, prasugrel) or warfarin with INR > 2 • Have cardiogenic shock (systolic blood pressure, SBP, < 80 mmHg), • Creatinine clearance < 30 mL/min using creatinine-based CKD-EPI equations • Elevated liver enzymes (3 times the upper normal limit) or liver cirrhosis • Uncontrolled hypertension (SBP > 180 mmHg), • Allergy, adverse drug reaction, or hypersensitivity to rivaroxaban or warfarin • Life expectancy < 6 months (e.g., metastatic cancer) • Women who are pregnant or of child-bearing age

*ADHF, acute decompensated heart failure; CRT, cardiac resynchronization therapy; ICD, implantable cardiac defibrillator implantation; ADP, adenosine-diphosphate; CKD-EPI, Chronic Kidney Disease Epidemiology Collaboration; SBP, systolic blood pressure; INR, international normalized ratio*.

* *Major surgical procedure or trauma within 30 days; history of major bleeding; clinically significant gastrointestinal bleeding within 180 days; chronic hemorrhagic disorder; intracranial neoplasm, arteriovenous malformation, or aneurysm; platelet count <90,000**/**μL*.

